#### Incident CKD

Among participants without pre-existing CKD at the index hospitalization, we will examine time to development of incident CKD with significant loss of renal function defined as experiencing both a minimum 25% reduction in level of eGFR compared with baseline and achieving CKD Stage 3 or worse[37] during follow-up.

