#### Baseline kidney function

To participate, all patients must have an available baseline pre-admission serum creatinine value, which is then used to estimate glomerular filtration rate (eGFR). A baseline serum creatinine value is defined as the outpatient, non-emergency department test result nearest to the index hospitalization. For the Kaiser Permanente and VALID Clinical Research Centers, the nearest value between 7 and 365 days before admission will be used, while for the TRIBE-AKI Clinical Research Center, the baseline serum creatinine can be present between 1 and 365 days before surgery, provided the patient is undergoing elective surgery. The rationale for this approach is based on preliminary data from the three Clinical Research Center networks demonstrating that the vast majority of potentially eligible participants do not have more than two to three pre-admission serum creatinine values during this time frame and that the most recent value is more likely to reflect the subject's "baseline" kidney function before the index hospitalization. All serum creatinine results must be performed using an isotope dilution mass spectrometry (IDMS)-traceable serum creatinine assay.

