### Definition of AKI

We recognize the limitations of the most recently proposed definitions for AKI (i.e., RIFLE[16] and Acute Kidney Injury Network [AKIN][17]), which are based only on changes in serum creatinine concentration and/or urine output. However, despite enthusiasm for potentially more sensitive and specific novel serum and urine biomarkers,[18] to date, none have been sufficiently validated as better measures of AKI or of subsequent prognosis than serum creatinine-based AKI criteria. A major goal of ASSESS-AKI is to provide key insights into the prognostic value of novel AKI biomarkers. Therefore, AKI will be operationalized as follows which is anticipated to capture a broad spectrum of kidney injury. For adult participants, AKI will be defined as ≥50% relative increase and/or absolute increase ≥0.3 mg/dL (26 μmol/L) in peak inpatient serum creatinine compared with baseline outpatient serum creatinine. For pediatric participants, AKI will be defined as ≥50% relative increase in peak inpatient serum creatinine compared with baseline serum creatinine. We did not incorporate urine output criteria from the AKIN classification scheme because of concern about the systematic availability and quality of data about urine output, especially in non-ICU patients who are unlikely to have indwelling urinary catheters. Furthermore, incorporating the urine output criteria for AKIN might overly enrich our cohort for patients with pre-renal azotemia.

To enhance the likelihood of enrolling an adequate number of adult participants with more severe AKI, we have set an enrollment target of at least one third of AKI participants having ≥100% relative increase in serum creatinine. To increase the probability of having an adequate number of adult participants with AKI due to causes other than rapidly reversible pre-renal azotemia, we have set an enrollment target of at least one third of AKI participants who meet AKI criteria lasting ≥48 hours. These additional enrollment targets are not mutually exclusive, and we anticipate significant overlap in these pre-specified subgroups. Furthermore, study nephrologists at each participating site will review selected index hospitalization information to classify each enrolled AKI case into one of the following presumptive categories: acute tubular necrosis (ATN), pre-renal azotemia, and other/unknown.

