### Definition of absence of AKI

Subjects will be considered not to have AKI if they meet the following criteria. For adult participants, non-AKI status will be defined as having both <20% relative increase and an absolute increase ≤0.2 mg/dL (18 μmol/L) in peak inpatient serum creatinine compared with baseline outpatient serum creatinine. For pediatric participants, non-AKI status will be defined as <50% relative increase in peak inpatient serum creatinine compared with baseline serum creatinine.

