#### Progression of CKD

Among participants with pre-existing CKD at the index hospitalization (defined as an eGFR <60 ml/min/1.73 m^2^), we will examine time to progression of CKD, defined as experiencing at least a 50% reduction in level of eGFR compared with baseline or progressing to CKD Stage 5 [37].

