One of the key challenges of existing studies relates to defining "baseline" kidney function for determination whether an episode of AKI has occurred and the severity of AKI [60,61]. A recent examination of this issue revealed that the use of imputed or commonly used surrogate estimates of baseline function can result in substantial misclassification of AKI and hinder adequate study of its associated outcomes [62]. Enrollment into ASSESS-AKI requires a pre-admission serum creatinine performed using an IDMS-traceable assay using a time frame recent enough to the index hospitalization that is likely to represent steady-state renal function and will substantially reduce the misclassification of the main exposure (i.e., occurrence of AKI) and of a key confounder (pre-admission CKD status) for enrolled participants, but it also creates barriers to participant recruitment. Many hospitalized patients who experience or are at risk for AKI may not have serum creatinine values available before the AKI episode, available values may not be performed using an IDMS-traceable assay, available values may be outside of our pre-specified time window (7 to 365 days before the index hospitalization), or values obtained during the eligible time window may not actually reflect steady-state renal function. All studies of AKI are affected by this challenge given that currently available consensus definitions of AKI are based on the magnitude of change of serum creatinine concentration. ASSESS-AKI will have strong internal validity given that both participants with and without AKI will have a consistently measured baseline measure of renal function that will serve as an anchor for assessment of longitudinal changes in kidney function.

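### One pre-admission creatinine sets both AKI status and the reference for incident CKD, so its error biases their association away from the null, by an amount that the documents cannot fix

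*Protocol article*

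**What the plan says.** All references are to the protocol article.

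- **Baseline kidney function:** "A baseline serum creatinine value is defined as the outpatient, non-emergency department test result nearest to the index hospitalization". The window is 7 to 365 days before admission (1 to 365 days before elective surgery in TRIBE-AKI). Part of the reason given for using one value is that "the vast majority of potentially eligible participants do not have more than two to three pre-admission serum creatinine values during this time frame".
- **Definition of AKI:** for adults, "≥50% relative increase and/or absolute increase ≥0.3 mg/dL (26 μmol/L) in peak inpatient serum creatinine compared with baseline outpatient serum creatinine".
- **Definition of absence of AKI:** for adults, "having both <20% relative increase and an absolute increase ≤0.2 mg/dL (18 μmol/L) in peak inpatient serum creatinine compared with baseline outpatient serum creatinine".
- **Initial screening and enrollment of participants:** pairs are matched on baseline CKD (eGFR below 60) and, where possible, on five categories of baseline eGFR.
- **Incident CKD:** among participants without CKD at the index hospitalization, "experiencing both a minimum 25% reduction in level of eGFR compared with baseline and achieving CKD Stage 3" or worse.
- **Progression of CKD:** "experiencing at least a 50% reduction in level of eGFR compared with baseline or progressing to CKD Stage 5".
- **Discussion:** the pre-admission value is a "consistently measured baseline measure of renal function that will serve as an anchor for assessment of longitudinal changes in kidney function", and this is offered as a reason for strong internal validity. The same paragraph concedes that a value in the window may not reflect steady state, but only as a difficulty in defining AKI.

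**The concern.** Exposure is the peak relative to baseline, and outcome is follow-up relative to baseline. Both use the same single reading, so its error enters both with the same sign. If the reading is below the patient's usual creatinine, an ordinary inpatient value looks like a rise and an ordinary follow-up value looks like a loss of eGFR. If it is above, both are hidden. The gap between the AKI and non-AKI thresholds separates the groups further on this error.

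The study aims to isolate the independent effect of AKI on later CKD. An association that arises partly from a shared denominator would be read as part of that effect. Measuring the baseline in the same way in both groups is no protection, because the classification rule itself sorts the errors between the groups.

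**Working it through.** **1. The plan's own figure.** Statistical approach and power states more than 80% power for N = 1,200 with 15% withdrawal. That leaves 600 × 0.85 = 510 per group. A two-proportion test at two-sided 0.05 gives:
- 30% vs 30/1.35 = 22.2% (difference 7.8 points): power 80.8%
- 10% vs 10/1.90 = 5.3% (difference 4.7 points): power 81.4%

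The statement reproduces. Each detectable relative risk belongs to a stated AKI event rate, which matters in step 5.

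**2. One patient.** Standard CKD-EPI coefficients are assumed. Take a man aged 60 with a steady true creatinine of 1.30 mg/dL and a pre-admission reading of 1.00.
- Baseline eGFR is 81.4.
- An unchanged inpatient 1.30 is a rise of 0.30, so he is AKI.
- An unchanged follow-up 1.30 gives eGFR 59.3. The fall is 1 − 59.3/81.4 = 27%, to Stage 3, so he has incident CKD.

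His kidneys did not change. The error is large: ln(1.30) = 0.262, or 2.6 SD at a CV of 10% and 3.7 SD at 7%. The case shows the mechanism and does not show its frequency.

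**3. Simulation with no AKI effect, true events rare.** From the protocol: the adult AKI, non-AKI and incident CKD rules, and the eGFR and age categories (non-AKI standardised to AKI). Assumed: 2 million adults per scenario; true eGFR mean 78, SD 20; fully recovering true rises in 15% or 30%; CV 6% for inpatient and follow-up values; three inpatient and four annual values; 2% yearly creatinine drift in everyone.

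| Baseline CV | AKI | Non-AKI | RR, same value as reference | RR, second value as reference |
|---|---|---|---|---|
| about 0 | 0.31–0.33% | 0.31–0.32% | 0.99–1.06 | 1.04–1.07 |
| 5% | 1.77–1.89% | 1.25–1.27% | 1.42–1.49 | 1.05 |
| 8% | 4.81–5.87% | 2.04–2.06% | 2.36–2.85 | 1.16–1.21 |
| 10% | 7.64–10.13% | 2.28–2.34% | 3.35–4.33 | 1.30–1.43 |

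Without baseline error the RR is about 1, which isolates the cause. A second set-up, with different assumptions, gave 1.5–1.7 (CV 5%), 1.9–2.2 (7%) and 2.1–2.4 (10%). The direction agrees, but the size is sensitive to the assumptions.

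**4. Matching.** Replacing the protocol's eGFR categories with 5-ml bands of observed eGFR moved the RR from 1.49 to 1.47 (CV 5%) and from 4.33 to 4.35 (CV 10%), with true rises in 15%. At a given observed value, patients labelled AKI still have the higher true creatinine on average.

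**5. Dependence on the event rate.** Let a fraction e of both groups develop genuine CKD unrelated to AKI, and let a and c be the rare-event rates in AKI and non-AKI. Approximately, RR = [e + (1 − e)a] / [e + (1 − e)c].

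| CV | a, c | e = 10% | e = 25% |
|---|---|---|---|
| 5% (step 3) | 1.89%, 1.27% | 0.1170/0.1114 = 1.05 | 0.2642/0.2595 = 1.02 |
| 7% (second set-up) | 3.1%, 1.4% | 0.1279/0.1126 = 1.14 | 0.2733/0.2605 = 1.05 |
| 10% (second set-up) | 14.0%, 5.7% | 0.2260/0.1513 = 1.49 | 0.3550/0.2928 = 1.21 |

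Full simulations agree broadly:
- Genuine CKD in 10% or 25%: 1.00–1.01 (CV 5%), 1.06–1.14 (7%), 1.24–1.51 (10%).
- Genuine variation in decline, matching in 5-ml bands, event rate 5–15%: 1.06–1.14, 1.16–1.30, 1.40–1.76. At event rates of 20–32%: 1.02–1.26.
- A further run: 1.02, 1.11, 1.36 near a 10% event rate, and 1.01–1.11 near 30%.

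**6. Second value as reference at moderate event rates.** The 1.06–1.14, 1.16–1.30 and 1.40–1.76 of step 5 fell to 1.01–1.03, 1.04–1.07 and 1.13–1.20. In the further run 1.36 fell to 1.05.

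**7. Confirmed outcome.** Requiring two consecutive qualifying visits cut the spurious excess from 1.5 to 0.3 points (CV 7%) and from 7.2 to 2.1 points (CV 10%). With 10% genuine CKD the RR fell from 1.14 to 1.04 and from 1.51 to 1.38.

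**The case against.** **Size.** A reader might infer that the bias matches the effects the study is powered for, since 1.42 at a CV of 5% exceeds 1.35. The documents do not support that. The 1.35 belongs to an AKI event rate of 30%, whereas the 1.42 arises at event rates below 2%. At the event rates for which power is stated, the bias is small at 5% and modest at 7%. This objection stands. It also stands that the CV, the frequency of true rises and the drift are all assumed, and that the rare-event runs disagree at a CV of 10% (2.1–2.4 against 3.35–4.33).

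**Reach.** The primary outcomes also include death and cardiovascular events. These do not use this reference, and neither does ESRD. CKD progression does, but its simulation gave an RR of about 2 even without baseline error, so it cannot size this mechanism. The size is shown for incident CKD only.

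**Confirmation.** It would be too strong to say that confirming the outcome is useless. It cuts the absolute excess, but the baseline error persists at every visit, so bias remains.

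**Ordinary analysis-plan content.** A sensitivity analysis may well sit in an analysis plan that is not shown, and the Discussion admits residual bias in general terms. But the point is not a missing detail. The article fixes the shared reference and presents it as a strength.

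**Meaning of baseline.** Follow-up visits and retention strategies calls the three-month visit a baseline visit. But Incident CKD sets CKD status at the index hospitalization, and the Discussion names the pre-admission value as the anchor for change. The pre-admission reading is the natural one.

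**Conclusion.** The concern holds in direction and, within limits, in size. Sharing one creatinine between AKI status, matching and the outcome reference biases the AKI–incident CKD association away from the null, and matching on the observed value does not correct it.

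With no true AKI effect and assumed CVs of 5 to 10%, the spurious relative risk is about 1.4 to 4 when true events are rare, about 1.0 to 1.5 (up to 1.8 in one simulation) at event rates near 10%, and about 1.0 to 1.3 at 20 to 30%. It enters the powered range of 1.35 to 1.90 mainly near a CV of 10%. The documents give neither the creatinine error nor the expected incident CKD rate, so they do not show which case applies. The simulations cover adults only and assume no AKI effect; the net bias when a true effect is present was not simulated.

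A reader might go further and conclude that any observed AKI–CKD association would be an artefact. The documents do not support that: at low error or common events the bias is slight.

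**What to change.** - Keep the nearest value for classifying AKI and non-AKI.
- Among participants with two or more eligible outpatient values in the window, pre-specify an analysis of incident CKD, and of the other eGFR-change outcomes that share the reference, with the reference taken from another value. Report it beside the main result.
- Add decline from the three-month visit eGFR as a supporting analysis, labelled as a different estimand. It omits loss already present at three months, so it should not decide whether an AKI effect may be claimed; true non-recovery could otherwise be disallowed.
- Qualify the internal-validity statement in the Discussion by saying that an error in the shared anchor moves exposure and outcome in the same direction.

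**Cost.** Extraction of creatinine values already in the records, and two further analyses. Participants with a single value drop out of the first. The article gives two to three values as the usual upper limit, so it does not show how many participants have a second. Those with repeat tests may differ from the rest. Some bias remains, because the nearest value still sets AKI status and the eGFR group at entry: 1.13 to 1.20 at a CV of 10% and moderate event rates, and 1.30 to 1.43 when events are rare.

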#### Progression of CKD

Among participants with pre-existing CKD at the index hospitalization (defined as an eGFR <60 ml/min/1.73 m^2^), we will examine time to progression of CKD, defined as experiencing at least a 50% reduction in level of eGFR compared with baseline or progressing to CKD Stage 5 [37].

#### Development of ESRD

Development of ESRD after the 3 month follow-up visit will be defined as any of the following: (1) peritoneal dialysis or hemodialysis treatment at least once a week for at least 12 consecutive weeks, (2) receipt of a kidney transplant and/or (3) death while receiving dialysis.

#### Incident or recurrent episodes of AKI

We will attempt to ascertain incident and recurrent episodes of AKI. Based on available data collected during follow-up, we will use the same criteria described previously to define incident (among non-AKI participants) or recurrent (among AKI participants) episodes of AKI. However, we recognize that some study participants may be hospitalized at non-Clinical Research Center network facilities where complete medical and laboratory records may not be readily available (and where non-IDMS serum creatinine assays may be used), hindering accurate determination of whether observed changes in serum creatinine reflect progression of kidney dysfunction or a new episode of AKI. In such cases, we will pursue whether the hospitalizations included administrative diagnostic codes for AKI and acute dialysis treatments which are typically coded administratively and likely reflect more severe AKI episodes.

### Cardiovascular outcomes

To maximize future collaborations with other studies focused on kidney disease among adult populations, we have modelled our definitions after those used in the CRIC Study[38] and various longitudinal studies (Cardiovascular Health Study,[21] Atherosclerosis Risk in Communities[20] and Antihypertensive and Lipid Lowering Treatment to Prevent Heart Attack Trial[39]). The general approach will be to obtain self-reported and/or site-specific database information on potential outcome events and subsequently obtain information on qualifying *International Classification of Diseases, Ninth and Tenth Editions *(ICD-9 and ICD-10) codes at each site which will facilitate review of relevant medical records to adjudicate. The following outcomes are only relevant for the subgroup of adult participants given that they are extremely rare among children.

#### Coronary heart disease

Standard definitions will be used to classify a coronary heart disease event. This includes acute coronary syndromes such as unstable angina, non-ST-elevation myocardial infarction and ST-elevation myocardial infarction [40,41]. Myocardial infarction will be further classified according to recent international consensus guideline [42]. Sudden cardiac death will be obtained by mortality files and subject proxy contacts. It will be defined as either an unwitnessed death without another obvious cause or death occurring within one hour of the onset of ischemic symptoms per a proxy [43]. Silent myocardial infarction will be defined as new, pathologic Q waves on serial electrocardiograms (ECG)[44] among the subgroup of enrolled adult participants with the event date assigned as the mid-point between the relevant annual visits. Coronary artery revascularization will include either percutaneous coronary intervention with or without intracoronary stenting or coronary artery bypass surgery of one or more coronary blood vessels.

#### Heart failure

Heart failure will be based on hospitalizations for a clinical heart failure syndrome using relevant discharge diagnosis codes and confirmed based on Framingham Heart Study clinical criteria ascertained from medical records [45]. We will not require evidence of systolic dysfunction (e.g., left ventricular ejection fraction <40%) or diastolic dysfunction on echocardiography [46].

#### Cardiac Arrhythmias and Electrocardiographic Abnormalities

Arrhythmias and other ECG abnormalities will be based on serial ECGs using Minnesota Code definitions,[47] which have been used in epidemiological studies and have direct clinical applicability. These include development of atrial fibrillation, atrial flutter, left and right bundle branch block, atrioventricular conduction defects, and left ventricular hypertrophy among others.

### Cerebrovascular outcomes

Pertinent cerebrovascular disease outcomes include ischemic stroke and intracranial hemorrhage, and carotid endarterectomy. Ischemic stroke will be defined as acute development of a neurological deficit fitting a vascular distribution, lasting ≥24 hours, and no other evident etiology such as intracranial hemorrhage, vasculitis, tumor, or trauma [48,49]. Intracranial hemorrhage will require validation by brain imaging or pathologic evidence, and should have a documented history consistent with a stroke syndrome, diminished consciousness, or headache [50]. Carotid endarterectomy will include both surgical endarterectomy and balloon angioplasty with or without carotid stent placement.

### Peripheral arterial disease outcomes

Outcomes will include aortic aneurysm and lower extremity arterial revascularization or amputation for refractory ischemia. Lower extremity revascularization will include both percutaneous peripheral artery angioplasty and surgical arterial bypass procedures, and lower extremity amputation will include procedures performed for refractory ischemia. Hospitalizations for thoracic or abdominal aortic aneurysm dissection, rupture or repair (using percutaneous or surgical procedures) will be included.

### Mortality

Deaths will be identified primarily through surveys of subjects or their proxy contacts and review of medical records or death certificates, if available. We will also seek to obtain information on social security number from participants to conduct probability matches with Social Security Administration vital status files[51] and National Death Index[52] among the subset set of participants who are lost to follow-up. All-cause mortality will be the preferred outcome given known significant errors in assigning etiology [53].

### Statistical approach and power

The primary outcomes for the study are time-to-event outcomes, such as time to death, a renal event or a clinical cardiovascular event. Some of these events will be known exactly on a continuum and could be right-censored. Exact dates for the occurrence of some of the events, however, may only be known to occur within a specific time interval t_k_, k = 1, 2, 3, 4, 5 (t_1 _= 0-3 months, t_2 _= 3-12 months, t_3 _= 12-24 months, t_4 _= 24-36 months, t_5 _= 36-48 months). The endpoints of these five time intervals correspond to the planned in-person study visits. Therefore, the statistical analyses in these situations will invoke continuous time-to-event models that account for right-censored and interval-censored data.

The hazard function for a continuous time-to-event outcome is of the form

$$\lambda_{\text{ijk}}(\text{t};{\text{x}}_{\text{ijk}})=\lambda_{0}(\text{t})\exp({\text{x}}_{\text{ijk}}\beta )$$

where

(a) λ_ijk_(t; x_ij_) is the hazard function at time t with covariate vector x_ijk _for the k^th ^member of the j^th ^matched set within the i^th ^site, j = 1, 2,...,n_i_, and k = 0 (non-AKI), 1 (AKI),

(b) λ_0_(t) is the baseline hazard function,

(c) β is an unknown parameter vector, and

(d) x_ijk _is a vector of regressors of interest.

The regressors that will appear in x_ijk _for the primary statistical analyses are as follows using as examples different variables: binary indicator variables at month 0 for non-AKI/AKI status, CKD status, gender, Hispanic ethnicity, cardiovascular disease status, diabetes status and sepsis status; ordinal variables at month 0 for racial group (0 = white/European, 1 = Black/African American, 3 = Asian/Pacific Islander, 4 = Native American, 5 = Other/Admixed), eGFR (0 = 15 to 29, 1 = 30 to 44, 2 = 45 to 59, 3 = 60 to 89, 4 = 90-150) and albumin-to-creatinine ratio (0 = <0.15, 1 = 0.15 to 0.5, 2 = >0.5 to 1.0, 3 = >1.0 to 3.0, and 4 = >3.0), age (0 = 1 to 17, 1 = 18 to 39, 2 = 40 to 49, 3 = 50 to 59, 4 = 60 to 69, 5 = 70 to 79, 6 = 80 to 89).

The hazard model described above, however, is not the final form of the hazard model that will be applied in this study. Instead, the hazard model needs to account for (1) the dependency between an AKI subject and a non-AKI subject within a matched pair and (2) informative censoring. The occurrence of some of the renal and cardiovascular events may not be independent of the censoring event of death. For example, individuals who are censored because of death may have been at higher risk for renal and cardiovascular events. Therefore, a bivariate hazard function for the simultaneous modeling of the renal (or cardiovascular) event and death is invoked [54,55]. Let (T_ijk_, D_ijk_) denote the continuous time of a renal or cardiovascular event and the time of death, respectively, for the k^th ^member of the j^th ^pair within the i^th ^site, j = 1, 2,...,n_i_, and k = 0 (non-AKI), 1 (AKI). The bivariate hazard model is

$$\lambda_{\text{T,ijk}}(\text{t};{\text{x}}_{\text{ijk}})=\lambda_{\text{T0}}(\text{t})\exp({\text{x}}_{\text{ijk}}\beta_{\text{Ti}}+{\text{e}}_{\text{Tij}})\;\text{and }\lambda_{\text{D,ijk}}(\text{d};{\text{x}}_{\text{ijk}})=\lambda_{\text{D0}}(\text{d})\exp({\text{x}}_{\text{ijk}}\beta_{\text{Di}}+{\text{e}}_{\text{Dij}})$$

where the [e_Tij _e_Dij_]'s are independent and identically distributed according to a bivariate normal distribution with null mean vector and positive-definite variance matrix. The covariance between e_Tij _and e_Dij _represents the magnitude of the relationship between the occurrence of the renal (or cardiovascular) event and the censoring event of death. An estimated value of the covariance near zero indicates non-informative censoring, whereas an estimated value of the covariance distant from zero indicates informative censoring.

The sample size for the study is (1) 550 adult AKI subjects and 550 matched adult non-AKI subjects and (2) 50 pediatric AKI subjects and 50 pediatric non-AKI subjects, at the 3-month visit. For a two-sided, 0.05 significance level test of the relative risk equaling 1.0, the sample size of 1,200 yields greater than 80% statistical power, while allowing for a 15% withdrawal rate, for detecting a relative risk between 1.35 (when the event rate for AKI subjects is 30%) and 1.90 (when the event rate for AKI subjects is 10%).

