### Follow-up visits and retention strategies

The follow-up visit and contact schedule are summarized in Table 2. All recruited participants will be invited to an in-person baseline study visit at 3 months after the AKI episode for AKI participants or 3 months after hospital discharge for non-AKI participants. Participants will return annually for in-person follow-up visits. Participants will be contacted by telephone at the 6-month intervals between clinic visits to obtain information on study events, or updates on general health and contact information.

**Table 2 T2:** Summary of visit schedule and study components for the ASSESS-AKI Study

Schedule	Inpatient	Baseline	Year 1		Year 2		Year 3		Year 4	
Months	0	3	6	12	18	24	30	36	42	48
Type of Contact	Visit	Visit	Phone	Visit	Phone	Visit	Phone	Visit	Phone	Visit
Consent for inpatient visit and specimen collection	●									
Consent for long-term follow-up		●								
Update contact info	●	●	●	●	●	●	●	●	●	●
Inpatient medications	●									
Inpatient risk factors for AKI	●									
Outcome Events		●	●	●	●	●	●	●	●	●
Outpatient medications		●	●	●	●	●	●	●	●	●
Urinalysis with microscopy (adults)	●									
Urine dipstick (adults)		●		●		●		●		●
Height and weight		●		●		●		●		●
Blood pressure		●		●		●		●		●
Questionnaires										
Sociodemographic characteristics	●	●								
Lifestyle habits		●		●		●		●		●
Medical History		●		●		●		●		●
Quality of life and functional status		●		●		●		●		●
Cognitive function (adults)		●		●				●		
Electrocardiogram (adults)		●		●		●		●		●
Collect specimens for storage in biorepository	●	●		●		●		●		●
Random urine sample	●	●		●		●		●		●
Blood for DNA		●								
Serum		●		●		●		●		●
Plasma-EDTA	●	●		●		●		●		●
Plasma-citrate		●		●		●		●		●

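### Interval limits for undated events are tied to the planned visit months, so a late or missed visit can put an event in an interval that excludes its true time

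*Protocol article*

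**What the plan says.** The section on statistical approach and power divides the time-to-event outcomes into two kinds. Of the first it says: "Some of these events will be known exactly on a continuum and could be right-censored". The second kind is known only to fall in one of five intervals, t_1 to t_5, running 0-3, 3-12, 12-24, 24-36 and 36-48 months. The article then states: "The endpoints of these five time intervals correspond to the planned in-person study visits". For these events it plans "continuous time-to-event models that account for right-censored and interval-censored data".

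The follow-up section sets an "in-person baseline study visit at 3 months after the AKI episode for AKI participants or 3 months after hospital discharge for non-AKI participants", and then: "Participants will return annually for in-person follow-up visits". It adds: "Participants will be contacted by telephone at the 6-month intervals between clinic visits to obtain information on study events". Table 2 places these calls at months 6, 18, 30 and 42. It marks outcome events at each call, but no serum, urine or electrocardiogram.

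Two further passages bear on which events lack a date. Possible cardiovascular events are traced through codes at each site, to "facilitate review of relevant medical records to adjudicate". Silent infarction is identified from serial electrocardiograms, "with the event date assigned as the mid-point between the relevant annual visits".

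**The concern.** An event that only an assessment can reveal is known to lie between the last assessment at which it was absent and the first at which it was present. Planned months give those limits only if every visit is held, and held on time.

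- **Late visit.** CKD first found at a month-12 visit held at month 14 may have begun after month 12, yet t_2 ends at 12.
- **Missed visit.** CKD found at month 36 after a missed month-24 visit is known only to lie in 12-36. No single t_k expresses that, and t_4 (24-36) may exclude the true time.

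A likelihood interval that excludes the event time is wrong, not just wide. At stake is the course of risk after AKI, since describing the natural history is one of the study's stated goals. The AKI hazard ratio would also be affected if the two groups differed in how late they attend.

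**Working it through.** **1. The plan's own figure.** The article claims more than 80% power with 1,200 participants, 15% withdrawal and a two-sided 0.05 test, for relative risks from 1.35 (AKI event rate 30%) to 1.90 (AKI event rate 10%). Evaluable per group: 600 × 0.85 = 510. With p2 = p1/RR and p̄ the mean of the two rates,

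power = Φ{[(p1 − p2)√n − 1.96√(2p̄(1 − p̄))] / √(p1(1 − p1) + p2(1 − p2))}.

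- p1 = 0.30, p2 = 0.2222: (1.757 − 1.218)/0.619 = 0.871, power 80.8%.
- p1 = 0.10, p2 = 0.0526: power 81.4%.

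The claim reproduces (a Wald test on the log relative risk gives 80.1% and 79.7%). The interval limits do not enter it, so this point leaves the sample size alone.

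**2. Inputs for the check.** Planned visits at months 3, 12, 24, 36 and 48 come from the article. Visit delays, missed-visit rates and hazards do not, and are assumed. The projected 3 to 5% annual loss to follow-up is not a missed-visit rate and was not used as one.

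**3. Share of visit-detected events misplaced.** Simulation of 400,000 participants, constant hazard 0.01 per month, exponential delays at every in-person visit, annual visits missed at random. An event counts as misplaced if its true time lies outside the planned interval ending at the visit that found it.

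| Assumption | Simulated | Hand check |
|---|---|---|
| All visits held on time | 0% | 0% |
| Mean delay 0.5 month | 5% | 5 × 0.5/48.5 = 5% |
| Mean delay 1 month | 10% | 5 × 1/49 = 10% |
| Mean delay 2 months | 19% | 5 × 2/50 = 20% |
| 5% of annual visits missed | 4% | 0.05 × 33/48 = 3% |
| 10% missed | 7% | 0.10 × 33/48 = 7% |
| 20% missed | 14% | 0.20 × 33/48 = 14% |
| Delay 1 month and 10% missed | 16% | |
| Delay 2 months and 20% missed | 29% | |

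The hand check for delay takes five late windows over the lengthened follow-up. For missed visits, it takes the 33 months (3 to 36) in which an event can be carried past a missed visit to a later one.

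**4. Effect on estimates.** Second simulation: control hazard 5% per year, true hazard ratio 2.0 or 1.35, uniform delays, month-3 visit on time, planned-month intervals fitted. The misplaced share is about 8% with a 1-month mean delay, slightly lower than above because only four visits run late (4/46 = 9%).

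- Mean delay 1 month in both groups: months 3-12 collect 10 months of events, so that hazard is inflated by 10/9 = 1.11 (0.056 against 0.050). The hazard ratio is essentially unbiased.
- AKI group later by 1 month on average: hazard ratio 2.03 to 2.05 for a true 2.0, and 1.38 to 1.39 for a true 1.35. Hand check: one extra month on the 45 from month 3 to 48 gives 46/45 = 1.022.
- AKI group later by 2 months: 2.08 to 2.11, and 1.41. Hand check: 47/45 = 1.044.
- 10% of visits missed in both groups: first-interval hazard about 10 to 12% too low, last about 12% too high, hazard ratio essentially unchanged.

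**5. Phone contacts.** Omitting them replaces, say, 12-18 by 12-24. The wider interval still contains the event time, so they add 0% to misplacement.

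**The case against.** The strongest reply is that the sentence describes and does not prescribe. The schedule explains why interval censoring arises. Nothing in the article says that actual dates will be disregarded, or that an event found at month 14 will be coded 3-12. An interval-censored likelihood ordinarily takes participant-specific limits, and rules for late or missed visits are detail that a journal article may leave to the full protocol or analysis plan. Much of this stands: misplacement is a consequence of applying the text literally, not a certainty. But the article is not silent. It names five common intervals and ties their ends to planned visits, so the stated limits can fairly be corrected.

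Three stronger readings are tempting, and the article does not support them.

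- **Ignoring the phone contacts misplaces events.** It only widens intervals. Table 2 schedules no serum, urine or electrocardiogram at those contacts, so the study's own creatinine and ECG assessments cannot be made there. Most events that can be reported by phone should be datable from medical records, and deaths from records, death certificates or proxies.
- **The AKI hazard ratio is inflated.** That needs AKI participants to attend later than their matches, and no passage says they do. The 3-month visit is counted from the AKI episode in one group and from discharge in the other, but the article does not define time zero for the models, so neither a bias nor its direction follows.
- **Events will be misplaced in a known proportion.** With punctual, complete attendance the share is 0%.

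**Conclusion.** The point holds as a minor one. As written, the planned-month limits can exclude the true time of an event found at a late visit or at the first visit after a missed one. The exposed outcomes are those detected at in-person visits: CKD incidence and progression, and silent infarction. For silent infarction, the mid-point date inherits the same problem if the visits are taken at their planned months; fixing a mid-point also sits awkwardly with the interval-censored approach.

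Under assumed timing, about 4 to 19% of visit-detected events are misplaced when delay or missed visits act alone, and up to 29% in the worst combination tried. Interval-specific hazards shift by roughly 10 to 12% with a 1-month mean delay or 10% missed visits. The hazard ratio is essentially unaffected when timing is equal between groups. It is about 2 to 3% too high if AKI participants are one month later on average, and about 4 to 5% if two. All of this rests on assumed delays, attendance and constant hazards. The stated power is unaffected.

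**What to change.** Replace the fixed t_k by limits specific to each participant:

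- lower limit: the date of the last assessment at which the event could have been detected and was absent;
- upper limit: the date of the assessment at which it was first found;
- after a missed visit, the interval runs across the gap;
- right-censoring falls at the actual last assessment at which the event could have been detected.

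Keep the planned months only as a description of the schedule. Treat silent infarction in the same way instead of fixing a mid-point date. As a small gain in precision, use the actual dates of the month 6, 18, 30 and 42 calls as limits for reportable events whose exact date stays unknown.

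The cost is a change of wording and slightly more analysis work. Visit and contact dates are ordinary study data, the interval-censored models are already planned, and no extra data collection or participants are needed.
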